#### Run-in cycle 2nd visit

*•* A non-fasting blood sample of 10 ml will be collected for the determination of the cycle phase.

*•* Physical performance tests include aerobic performance, aerobic capacity, peak power output, isokinetic muscle strength, and jumping performance.

*•* For the detection of ovulation, the participants will use urinary sticks (Ovustix, Clearplan, Unipath Limited, Bedford, UK) measuring the luteinizing hormone (LH) surge.

#### Run-in cycle 3rd visit

*•* A non-fasting blood sample of 10 ml will be collected for the determination of the cycle phase.

*•* Physical performance tests include aerobic performance, aerobic capacity, peak power output, isokinetic muscle strength and endurance, and jumping performance.

*•* Randomization to one of the two intervention groups or control group.

### Intervention

#### Explanation for the choice of comparators {6b}

In this randomized controlled trial, we have chosen to include well-trained females and will randomly assign them to the regimen of extended sessions of exercise during the follicular phase or during the luteal phase in the menstrual cycle and the control group of regular exercise throughout the menstrual cycle. All participants irrespective of intervention group or control will over the total intervention period obtain the same numbers of training sessions.

#### Intervention description {11a}

The participants will be randomized to different training scheduling of spinning and strength training during the following three menstrual cycles (Fig. 2).

**Fig. 2 Fig2:**
[figure not shown]
The disposing of spinning exercise and strength training in the two intervention groups (**A**, **B**) and the control group (**C**) in an average 28-day menstrual cycle

*Group A*: follicular phase-based training (spinning and strength training) five sessions per week during the follicular phase (approx. 14 days) and thereafter once a week during the luteal phase (approx. 14 days)*Group B*: luteal phase-based training (spinning and strength training) once a week during the follicular phase (approx. 14 days) and thereafter five sessions per week during the luteal phase (approx. 14 days) *Group C*: regular training (spinning and strength training) three times a week throughout the study period (control group)

In total, there will be 12 sessions of exercise per menstrual cycle during 3 consecutive cycles for all 3 groups.

At the end of the run-in cycle, randomization will be performed, and the participants will start the intervention immediately, at the following first day of menstruation. The intervention lasts for 3 menstrual cycles. The training program during the intervention consists of spinning exercise and muscular strength training, at the training centers in the Stockholm area, Sweden. The spinning exercises consist of 55 min of intermittent, high-intensity training (75–90 percent of maximal heart rate) with recovery periods in between. The heart rate during the spinning will be followed and registered on each occasion during the study period. Additionally, during at least 1 session per week, the total work in Joule will be monitored, utilizing a Wattbike during the exercise, and participants will be responsible for reporting these values in the REDCap® system. The strength training program consists of five exercises for the lower body (squats, lunges, hip thrust, and for core muscles back extension and isometric trunk, e.g., “plank”). The load and the number of repetitions of the strength training will be based on the participants’ fitness level and tested out during the run-in cycle. The range of repetition will be within 8–12 repetitions, and the number of sets will range within two to four sets.

During every training session, the participants will register their perceived exertion as well as the rating of perceived motivation prior to exercise in the REDCap®. To confirm the specific phase of the menstrual cycle, blood samples will be collected according to the EFP, LFP, and MLP (Fig. 1).

#### Criteria for discontinuing or modifying allocated intervention {11b}

The participants will have the full right to discontinue the intervention and their study participation at any time, without having to explain the reason. In case of temporary illness (e.g., cold or flu) that causes the inability to exercise, the intervention period will be extended. The decision about the extension of the intervention period is made in each individual case by the project management group. If a participant develops symptoms and signs of mental and/or physical illness during the assessment of physical tests or during the intervention, the formal stopping rules will apply. Modification of allocated intervention will not be made.

#### Strategies to improve adherence to intervention {11c}

Adherence to this protocol is judged to be high, as it does not consist of very strict guidelines. Strategies to improve adherence to the intervention protocol include reminders by a daily text message to each participant. To evaluate the amount of exercise completed by every participant, each training session will be documented (attendance, total time of exercise, average heart rate, perceived exhaustion, and motivation prior to exercise).

#### Relevant concomitant care permitted or prohibited during the trial {11d}

The use of regular medication during the study is not permitted, but temporary use of, e.g., analgetic due to headache could be allowed based on individual judgment. Other treatments will not be allowed.

During the intervention period, the participants are not allowed to carry out heavy or intense training (above scale number 12 on the Borg RPE scale) apart from the training schedule given by allocation. The participants are free to take part in light daily activities, like commuting to work by bike or walking.

#### Provisions for post-trial care {30}

There is no anticipated harm and compensation for trial participation. This study focuses on health and wellness, and all participants will be given the same amount of training throughout the trial. There is no provision for post-trial care.

### Outcomes {12}

#### The primary and secondary outcomes assessed at baseline and at follow-up at week 17

The outcome measures are listed in Table 2. The primary outcome measure is the aerobic performance of cycling time to exhaustion (TTE) during an individually incremental workload on a cycle ergometer. Secondary outcome measures are aerobic capacity of gas exchange (VO_2max_) on a cycle ergometer, 4000-m self-paced cycling time trial (TT), muscle strength (isokinetic peak torque), jumping performance (countermovement jump), ratings of menstrual-related symptoms, body composition, and muscle tissue variables (in a sub-sample of participants).

**Table 2 Tab2:** Outcome measures

Outcome	Instrument	Domains	Unit
*Laboratory test*			
Time to exhaustion (TTE)*	Incremental cycle ergometer test	Aerobic capacity and exhaustion	Time in min:s
VO_2max_	COSMED, incremental cycle ergometer test	Aerobic capacity, and gas exchange	ml O_2_/kg/min
Submaximal VO_2max_	Åstrands test	Aerobic capacity	Estimated ml O_2_/kg/min
4000-m cycling time trial	4000-m cycle ergometer test	Aerobic capacity	Time in min:s
Isokinetic muscular strength	Biodex at 60°/s	Muscular strength, knee extensors, and knee flexors	Newton meter (Nm) peak torque
Fat mass, fat-free mass, mineral density	Dual-energy X-ray absorptiometry (DXA)	Body composition	Mass and density
Muscle morphology	Weil-Blakesley conchotome, muscle biopsy	Muscle morphology	
Blood markers	Blood sampling	Blood cells, genetics, biochemistry, and hormonal levels	
Capillary blood lactate	Blood sampling	Lactate	mmol/l
*Clinical test*			
Hop function	Countermovement jump	Explosive muscular function	Centimeters (cm)
*Questionnaires*			
Effort perception	Borg scale		Scale number of perceived exhaustion (6–20)
Premenstrual symptoms	Daily Record of Severity of Problems (DRSP)		Scale number of severity (1–6)
Dysmenorrhea	Numerical Pain Rating Scale (NRS)		Scale number of severity (0–10)
*Free-living assessment*			
Numbers of daily steps	Oura smart ring	Physical activity	Numbers (*n*)
Quality of sleep	Oura smart ring	Sleep pattern	

*Primary outcome measure

### Participant timeline {13}

The time schedule of enrollment, intervention, assessments, and visits of participations is shown in a schematic diagram in Fig. 3a, b.

**Fig. 3 Fig3:**
[figure not shown]
**a** Flowchart and participant timeline. Schedule of enrollment, interventions, and assessments. Time point in the figure: − *t*_1_ = approx. 6 weeks prior to allocation (0), *t*_1_ = weeks 1–4 (2nd menstrual cycle), *t*_2_ = weeks 5–8 (3rd menstrual cycle), *t*_3_ = weeks 9–12 (4th menstrual cycle), and *t*_4_ = week 13. The time points refer to an average 28-day menstrual cycle. * Physical tests = test of aerobic capacity and performance and muscle strenght and jump performance. ** Outcome measures = all outcome measures listed in table 2. **b** Schedule of enrolment, interventions, and assessments according to SPIRIT guidelines 2013. Timepoint in the figure: -t1 = approx. 6 weeks prior to allocation (0), t1 = week 1-4 (2nd menstrual cycle), t2 = week 5-8 (3rd menstrual cycle), t3 = week 9-12 (4th menstrual cycle), t4 = week 13. The timepoints is based on a 28-day menstrual cycle

### Sample size {14}

The power estimation was conducted using the R statistical software (the R Foundation for Statistical Computing, Vienna, Austria), package “SIMR.” To identify an effect size difference of 0.70 SD in TTE (primary outcome), between two of the groups, 33 individuals need to be included in each group (alpha 0.05, power 80%). For the secondary outcomes, an effect size difference of 0.60 SD is assumed. This results in that 36 individuals should be included in each group. Assuming dropouts (*n* = 12), 40 individuals will be included in each group, which will give an allocation ratio of 1:1. No power calculation is performed for the exploratory outcomes such as muscle tissue variables.

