## Discussion

The impact of the menstrual cycle on training and physical performance is still not elucidated. Although previous studies on periodized training indicate an eventual advantage for follicular-based training [3], the results are not conclusive. Furthermore, the role of menstrual cycle-related symptoms for training and performance has not been fully explored. A recent study suggested that motivation to exercise is of superior significance rather than variation in hormone levels during the menstrual cycle to improve physical performance [4]. As several menstrual cycle-related symptoms such as dysmenorrhea and PMS are common among athletes, these symptoms might affect motivation and the effectiveness of training sessions.

With a robust methodology and sufficient sample size, the IMPACT study has the potential to provide evidence of the effect of exercise periodization during different phases of the menstrual cycle, which could form the basis for recommendations of training to improve physical performance and maintain health in female athletes. The rationale for the study procedures relies on the findings and recommendations from earlier studies [3]. During the IMPACT study, the included women will be followed prospectively for four consecutive menstrual cycles and be continuously examined during the study period. Besides the main outcome of aerobic capacity, a broad range of comprehensive examinations of physiological, mental, and behavioral parameters will be collected, which will provide opportunities to thoroughly explore potential variables that impact physical performance and trainability in female athletes.

To confirm the menstrual cycle phase, blood and urine samples will be collected throughout the study period for hormone determination. Additionally, the subjects will rate and report their menstrual symptoms, e.g., PMS and dysmenorrhea on a daily basis. The online tool REDCap® will be utilized to send out messages to the participants requesting daily ratings and reminders in case of missing replies. This will lead to more accurate reporting compared to retrospective ratings.

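### The 36 per group for 0.60 SD in the secondary outcomes does not follow from the inputs that give 33 per group for 0.70 SD; the same rule needs about 45.

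*Protocol article*

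**What the plan says.** Under Sample size {14}, the article says that power was estimated in R with the package SIMR. The primary calculation is introduced with "To identify an effect size difference of 0.70 SD in TTE (primary outcome), between two of the groups" and concludes that "33 individuals need to be included in each group", with "alpha 0.05, power 80" per cent given in brackets.

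The next two sentences turn to the secondary outcomes: "an effect size difference of 0.60 SD is assumed. This results in that 36 individuals should be included in each group". No other alpha, power, sidedness, correlation or model is given for this second figure. Twelve dropouts are then added to reach 40 per group.

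Statistical methods {20a} plans linear mixed models for primary and secondary outcomes alike, with one significance level, p < 0.05. The Discussion describes the trial as having "With a robust methodology and sufficient sample size".

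**The concern.** Between the two calculations only the effect size changes, and it falls by one seventh. Required sample size varies with the inverse square of the effect size, so the number per group should rise by about 36%. The printed figures rise by 9% (36/33 = 1.09). Both cannot be right under the inputs given.

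The 36 is also the figure that sets enrolment: 3 x 36 = 108, plus 12 dropouts, makes 120, or 40 per group.

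What is at stake is how null secondary results will be read. The secondary outcomes include VO2max, the 4000-m time trial, isokinetic strength and jump height, and muscle strength is named in the primary hypothesis under Objective {7}. A reader who takes 80% power at face value expects a true 0.60 SD difference to be missed one time in five. If power is about 71%, it is missed about 29% of the time, and a non-significant result says less than it seems to.

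**Working it through.** **Inputs.** From Sample size {14}: alpha 0.05; power 80%; 0.70 SD with 33 per group; 0.60 SD with 36 per group; 12 dropouts; 40 enrolled per group. Not stated: sidedness, within-person correlation, variance components.

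**Step 1. Reproduce the primary figure.** For two equal groups, with d the difference in SD units, the normal approximation is n = 2(z_alpha + z_power)² / d².
- Two-sided: 2 x (1.960 + 0.842)² / 0.70² = 15.70 / 0.49 = 32.0, rounded up to 33. The t-test solution is 33.02, and power at n = 33 is 79.97%. The stated 33 is reproduced.
- One-sided, the figure would be 26, which does not match.

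**Step 2. Apply the same rule at 0.60 SD.**
- Normal approximation: 15.70 / 0.36 = 43.6, rounded up to 44.
- t-test: 44.6, rounded up to 45.
- Scaling the article's own figure: 33 x (0.70/0.60)² = 44.9.
- In reverse: 36 x (0.60/0.70)² = 26.4 at 0.70 SD, not 33.

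The scaling check does not depend on the test chosen, provided alpha, power, sidedness and correlation are the same for both outcomes. A three-group ANOVA in which one group differs gives 30.5 and 41.2 per group, so it does not produce the pair either.

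**Step 3. What the planned numbers deliver (two-sided 0.05, two-sample t-test).**

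| Completers per group | Power at 0.60 SD | Power at 0.70 SD | Detectable with 80% power |
|---|---|---|---|
| 36 | 70.9% | 83.4% | 0.67 SD |
| 40 | 75.5% | 87.1% | 0.63 SD |
| 45 | 80.4% | 90.7% | not computed |

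Using the error degrees of freedom of all three arms raises the 70.9% only to 71.3%.

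**Step 4. Unstated assumptions that would give 36 at 0.60 SD.**
- One-sided 0.05, 80% power: t-test 35.04, rounded up to 36.
- Two-sided 0.05, 70% power: t-test 35.27, rounded up to 36.
- Two-sided 0.05, 80% power, change scores: the variance factor is 2(1 - rho). Setting 44.6 x 2(1 - rho) = 36 gives rho of about 0.60.
- Two-sided 0.05, 80% power, baseline-adjusted comparison: the factor is 1 - rho². Setting it to 36/45 gives rho = 0.45; 36/44 gives 0.43.

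Each of these, applied to both outcomes alike, would lower the primary figure to about 26, so none gives 33 and 36 together.

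**The case against.** The strongest reply is that SIMR simulates mixed models. In such a model the sample size depends on the within-person correlation as well as the effect size, and time to exhaustion, VO2max, torque and jump height need not share one correlation. Nor does the match of 33 to a simple t-test show that correlation was ignored: with change scores the factor 2(1 - rho) equals 1 at rho = 0.50, so that correlation also gives 33 at 0.70 SD. A correlation of 0.50 for the primary outcome and about 0.60 for the secondary outcomes would therefore reproduce both figures, two-sided at 80% power. These correlations are assumptions; the article gives none.

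This part of the reply stands. A reader might infer from Step 4 that a one-sided test was used for the secondary outcomes, so that the two figures rest on different error rates, or that 36 cannot be an 80% power figure at all. The article supports neither inference: it states no sidedness, and at least two other routes lead to 36.

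It is also fair that the 80% is printed beside the primary outcome and not repeated. Carrying it over is a reading, though the natural one, since the next sentence presents 36 as the result of the new effect size alone. The Discussion's remark on sample size is general and does not mention secondary outcomes, so little weight rests on it.

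The argument that a condensed article may leave simulation inputs to the full protocol does not dispose of the point. The complaint is not that detail is absent, but that two printed figures disagree under the printed inputs.

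**Conclusion.** The point holds, as an inconsistency between two printed figures. Under the rule that reproduces the primary figure (two-sided 0.05, 80% power, two groups compared, no difference in correlation between outcomes), 0.60 SD needs about 45 per group, 9 more than stated. On the same rule, power at 0.60 SD is about 71% with 36 completers. Even with no dropouts it stays below 80%.

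The 71% is conditional on that rule. If the simulation gave the secondary outcomes a higher correlation than the primary outcome, 80% could be correct, but the text would then have to say so. Which explanation applies cannot be settled from the article.

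Severity is moderate. The sentence is wrong as written and sets the enrolled number, but the primary outcome is not underpowered: the 36 exceeds the 33 it requires and gives about 83% power at 0.70 SD. No analysis or decision rule depends on the secondary figure.

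**What to change.** Do not enrol more women. Correct the sentence on the secondary outcomes in one of two ways.

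1. If the inputs were the same for both calculations, restate the figure, for example: *With 36 completers per group, the trial has 80% power (two-sided alpha 0.05) for a difference of 0.67 SD in a secondary outcome, and about 71% power for 0.60 SD.*
2. If the SIMR run used different inputs for the secondary outcomes, state them (sidedness, power, baseline-to-follow-up correlation), and use the same sidedness for both figures. If that means recomputing one of them, print the recomputed value.

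In either case, state the sidedness of the 0.05 level once for both calculations.

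The cost is one or two sentences in the sample size section. Under the first option the stated sensitivity for the secondary outcomes becomes slightly less favourable; enrolment, the primary calculation and the analysis stay as they are.

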### Recruitment {15}

The participants will be recruited via advertisement at the Karolinska Institutets (KIs)s website for research subjects, via a student’s platform at KI medical education and at the Swedish School of Sports and Health Sciences. Recruitment announcements will be posted online and at sports and healthcare universities in the Stockholm area, Sweden.

### Assignments of interventions: allocation

#### Sequence generation {16a}

A computer-generated random number list (allocation table), aiming to randomly order the participants to the three study groups, will be prepared by a statistician with no involvement in the trial.

#### Concealment mechanism {16b}

Allocation is not concealed and will be revealed to both the participant and the researcher upon randomization.

#### Implementation {16c}

The allocation sequence is generated by a statistician with no involvement in the trial. The REDCap® randomization module will be utilized to implement and upload the allocation table in the system as well as allocate the participant to one of the three groups. The study group will be revealed at the same time for both participant and researcher.

### Assignments of interventions: blinding

#### Who will be blinded {17a}

Blinding of intervention for the participants will not be possible for obvious reasons. Furthermore, the study coordinator will give individual instructions about the specific training program according to group distribution and individual cycle length. However, analysis of study outcomes will be performed by a researcher blinded to group allocation.

### Data collection and management

#### Plans for assessment and collection of outcomes {18a}

##### Settings

The physical performance tests will be performed at the u-MOVE laboratory for human movement and activity at the Karolinska University Hospital, Stockholm, Sweden. Prior to the data collection at baseline, the participants will visit the laboratory for familiarization tests and to determine performance values.

##### Aerobic capacity and aerobic performance on cycle ergometer test

A submaximal cycle ergometer test described by Åstrand [21] will be performed followed by a progressive test of maximal aerobic capacity (VO_2max_). The protocol for VO_2max_ will be performed by incremental cycling on an electric braked cycle ergometer (Monark 928 G3). The participants will start at 125–150 W (depending on pretest results) and increase 10 W every 20 s until exhaustion, and the cadence drops below 30 revolution per minute (RPM). The primary outcome measure (TTE) will be registered on a separate timer, from the start of the cycling protocol to the point of exhaustion when the test stops. Oxygen uptake and carbon dioxide elimination will be measured by the breath-by-breath method (BxB mode) and together with workload and heart rate will be recorded continuously throughout the test. A portable metabolic system COSMED (K5) will be utilized to measure oxygen consumption (VO_2_) and carbon dioxide production (VCO_2_). The COSMED K5 in BxB mode is considered a valid system for the measurement of ventilation (VE), VO_2_, and VCO_2_ for a wide range of metabolic rates [22]. Rating of perceived exertion (RPE) will be monitored using the Borg RPE scale [23]. The variable for aerobic capacity for gas exchange is measured by ml 0_2_/kg/min.

##### 4000-m self-paced cycling time trial (TT)

The 4000-m self-paced cycling TT [24] will be performed on a cycle ergometer (Monark 928 G3). The participants will start with 3 min cycling at 125 W and then further 3 min at 70% of VO_2peak_. After this 6-min warm-up, the participants will be given a 5-min rest to prepare for the subsequent time trail. The participants will be given the instruction to complete the distance of 4000 m in as short time as possible. Verbal feedback on the distance covered every 400 m will be given, and the heart rate will be recorded at those time points. The participants will be allowed to adjust the gear to a preferred cadence during the trial. A capillary blood sample will be obtained and assessed for lactate (La) concentration immediately after completing the test and at 7 min posttest.

